### **7.2 Data entry**

All data will be double-entered by two study group members, and will be collected at two databases for consistency. Whenever inconsistencies are found, the data will be rechecked by re-examination according to original CRFs or medical history.

## **8. Statistical Consideration**

### **8.1 Sample size calculating**

There are no studies evaluating the long-term prognosis of LBBP, and results for the long-term prognosis of BVP vary among studies. Therefore, the data for the sample size estimation of this study are mainly derived from our preliminary clinical experience. A sample size of 190 patients is calculated to detect a statistically significant difference in the primary endpoint with 80% power and two-tailed alpha

level of 5%, assuming 10% event rate in the LBBP and 25% in the BVP arm with 10% dropout and 5% crossover. To ensure sufficient statistical efficiency, the sample size is finally determined to be 100 for each group.

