## **6. Interventional method**

### 6.1 Procedural of LBBP

LBBP will be performed as following steps: (1) the His bundle (HB) potential will be first mapped with the pacing lead through the sheath; (2) then the lead is moved from the HB potential location towards the right ventricular apex for approximate 1 to 2 cm under the right anterior oblique (RAO) 30° fluoroscopic view and is deeply screwed into the interventricular septum (IVS); (3) LBBP is considered to be successful if the

unipolar paced QRS morphology demonstrate a right bundle branch block (RBBB) pattern and meet any of the following criteria: 1) Paced morphology changes between selective LBBP and nonselective LBBP with constant left ventricular activation time (LVAT); 2) Paced morphology changes from left ventricular septal pacing (LVSP) to nonselective LBBP with LVAT abruptly shortening by increasing pacing output. Crossover will be allowed when LBB capture could not be achieved.

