## 6.2 Procedural of BVP

BVP will be performed with a standard fashion and lateral or posterolateral branches are preferred choices for LV lead implantation, quadripolar LV lead is also used whenever feasible. Crossover will be allowed when the LV lead implant unsuccessfully due to anatomical variations, high pacing threshold, or phrenic nerve stimulus.

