## **11. Statistical consideration**

### **11.1 Sample size calculating**

There are no studies evaluating the long-term prognosis of LBBP, and results for the long-term prognosis of BVP vary among studies. Therefore, the data for the sample size estimation of this study are mainly derived from our preliminary clinical experience. A sample size of 190 patients is calculated to detect a statistically

significant difference in the primary endpoint with 80% power and two-tailed alpha level of 5%, assuming 10% event rate in the LBBP and 25% in the BVP arm with 10% dropout and 5% crossover. To ensure sufficient statistical efficiency, the sample size is finally determined to be 100 for each group.

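### The 190 patients said to give 80% power with 10% dropout and 5% crossover cannot be reproduced from the stated inputs; read as risks over full follow-up, 200 patients give about 70 to 76%

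*Supplement*

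**What the plan says.** The sample size paragraph is the same in SAP 8.1 and protocol v1.1 section 11.1. It states: "A sample size of 190 patients is calculated to detect a statistically significant difference in the primary endpoint with 80% power". The inputs are a two-tailed alpha of 5%, "assuming 10% event rate in the LBBP and 25% in the BVP arm with 10% dropout and 5% crossover". For a margin, "the sample size is finally determined to be 100 for each group".

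No formula or software is named. Neither the period over which 10% and 25% of patients have an event nor the direction of the crossover is given, and it is not said whether 5% applies to each arm or to the whole trial.

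Four other parts of the plan bear on the calculation:

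- The clinical endpoints are compared by a log-rank test (SAP 8.4), and all analyses follow intention to treat (SAP 8.3).
- Crossover can occur both ways. Protocol 6.1: "Crossover will be allowed when LBB capture could not be achieved". Protocol 6.2: "Crossover will be allowed when the LV lead implant unsuccessfully due to anatomical variations".
- Visits continue every six months with no stated last visit (protocol 4.1 and 7, SAP 3).
- The study lasts about 4 years, of which 1.5 are recruitment (protocol 16).

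**The concern.** The contrast of 10% v 25% is a familiar one, and about 100 per arm is what it needs with complete follow-up and full adherence. A figure of 190 that is said to absorb dropout and crossover as well is therefore smaller than expected. Under intention to treat, crossover pulls the two arms' event rates together, so it costs more than the same percentage of lost patients.

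At stake is how a null primary result is read. The plan promises a 20% chance of missing the target difference. If the real chance is nearer 24 to 30%, a null result would be given too much weight as evidence against that difference.

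**Working it through.** **Inputs (SAP 8.1).** p1 = 0.10 (LBBP), p2 = 0.25 (BVP), two-sided alpha 0.05 (z = 1.960), power 0.80 (z = 0.842), 1:1 allocation, dropout 10%, crossover 5%. (1.960 + 0.842)² = 7.849. In steps 1 to 4 the rates are taken as cumulative risks over follow-up.

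**1. No allowances.**

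- Unpooled proportions: n per arm = 7.849 × (0.10×0.90 + 0.25×0.75) / 0.15² = 7.849 × 0.2775 / 0.0225 = 96.8; total 194.
- Pooled proportions: n per arm = [1.960·√(2×0.175×0.825) + 0.842·√0.2775]² / 0.0225 = 99.5; total 199.
- Schoenfeld log-rank: HR = ln 0.90 / ln 0.75 = 0.366; events = 4 × 7.849 / (ln 0.366)² = 31.1; N = 31.1 / 0.175 = 178.

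**2. Dropout only (divide by 0.9).** 215, 221 and 198.

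**3. Both allowances.** With 5% crossover in each arm, the intention-to-treat rates become 0.95×0.10 + 0.05×0.25 = 0.1075 and 0.95×0.25 + 0.05×0.10 = 0.2425. The other rows change the rates in the same way. Totals include division by 0.9.

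| Reading of 5% crossover | Rates compared | Two proportions (unpooled, pooled) | Schoenfeld |
|---|---|---|---|
| 5% in each arm | 10.75% v 24.25% | 268, 274 | 250 |
| 5% LBBP to BVP only | 10.75% v 25% | 244, 250 | 227 |
| 2.5% in each arm | 10.375% v 24.625% | 239, 245 | 222 |
| 5% BVP to LBBP only | 10% v 24.25% | 235, 241 | 217 |

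The plan's 190 is not reproduced. Two-sided calculations come close only when an input is left out: 194 is the unpooled number with no allowance, and 178 × 1.1 = 196 is Schoenfeld with dropout and no crossover. One-sided tests with crude inflation give 185 to 192, but the plan says two-tailed.

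**4. Power at the planned size.** Schoenfeld power is Φ(√events × |ln HR| / 2 − 1.960). For 200 enrolled and 5% crossover in each arm, events = 180 × 0.175 = 31.5 and HR = 0.4095, so power = Φ(2.506 − 1.960) = 71%. The simulated log-rank figures use exponential event times, with 10% of patients dropping out uniformly over follow-up (8,000 runs per cell).

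| Reading of 5% crossover | N = 190: Schoenfeld, simulated | N = 200: Schoenfeld, simulated |
|---|---|---|
| 5% in each arm | 69%, 67% | 71%, 70% |
| 5% LBBP to BVP only | 73%, 72% | 75%, 73% |
| 2.5% in each arm | 74%, 73% | 76%, 75% |
| 5% BVP to LBBP only | 75%, 73% | 77%, 75% |

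The first row at N = 200 yields about 33 events in simulation. Under that row's assumptions, 80% power at 200 is reached for 25% v about 8.5%.

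**5. If the rates refer to a shorter horizon (assumption).** With uniform accrual over 1.5 years and closure at 4 years (protocol 16), each patient is followed for 2.5 to 4 years if follow-up runs to study end. Simulated log-rank power with 10% dropout and 5% crossover in each arm:

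| Horizon of 10% and 25% | N = 190 | N = 200 | Events at 200 |
|---|---|---|---|
| 2 years | 85% | 87% | about 50 |
| 2.3 years | 81% | 83% | about 45 |
| 2.5 years | 78% | 80% | about 42 |
| 3 years | 71% | 74% | about 36 |
| 3.25 years (mean follow-up) | 68% | 70% | about 33 |

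**The case against.** The strongest answer is the missing horizon. The primary test is a log-rank test and follow-up has no stated end, so events may accrue beyond whatever period the 10% and 25% describe. Step 5 shows that a horizon of about 2.3 years would give about 80% even at 190, with both allowances and the harshest crossover reading. A log-rank calculation with accrual and follow-up is a standard method, so it cannot be said that no standard method yields 190. This stands, and it limits the conclusion. It does not rescue the paragraph, which states no horizon, accrual or follow-up and names no such method.

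Crossover is also open to interpretation. The 5% may be a trial-wide total or apply to one direction. That too stands, and it moves power at 200 from about 70% to about 74 to 76%, still short of 80% on the full follow-up reading.

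A third answer is that the rates may already be net of crossover. Then only dropout matters, and Schoenfeld gives 78% at 190 and 80% at 200. But the sentence lists crossover beside dropout as a separate allowance, so this is not the natural reading.

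Finally, 200 may be called a safety margin. It adds 10 patients, while the most lenient route in step 3 needs 217.

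A reader might infer that the trial simply has 70% power and a 30% miss rate. The documents do not support that as a flat statement: it needs both the full follow-up reading and 5% crossover in each arm, and the plan states neither.

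**Conclusion.** The point holds in conditional form. With the rates read as cumulative risks over follow-up, which is the ordinary reading of a sample size paragraph with no horizon, 190 does not follow from the printed inputs and 200 falls short of 80% under every crossover reading tried. The shortfall in patients at 200 is about 17 to 50 by Schoenfeld and 35 to 74 by two proportions. In power it is about 4 to 10 percentage points.

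These figures rest on proportional hazards, 10% dropout in both arms, and crossed-over patients taking the risk of the device they received. If the rates refer to about 2.3 years or less and everyone is followed to study end, the shortfall disappears; at 2.5 years power at 200 is right at the 80% mark. The supportable fault is a sample size statement that its own inputs do not deliver as written and that cannot be checked without details the plan omits. It is not proof that the trial is underpowered.

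**What to change.** In protocol section 11.1 and SAP 8.1, keep 200 patients and remove the statement that 190 give 80% power with both allowances. State:

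- the method (log-rank);
- the follow-up time to which 10% and 25% refer;
- the accrual period and the length of follow-up assumed;
- whether 5% crossover applies to each arm, to one direction or to the trial as a whole.

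Then restate the power and expected number of events that follow from those choices. If the rates are cumulative over full follow-up with 5% crossover in each arm, the text would give about 70% power with about 33 events for 25% v 10%, and about 80% power only for 25% v about 8.5%. These numbers should not be written in before the horizon is fixed, because they depend on it.

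The cost is a change of wording in two documents and possibly a less favourable stated power. No extra patients are needed.

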## 8.2 Results description

Continuous variables are described as mean  $\pm$  SD and categorical variables are described as frequencies or percentages.

## 8.3 Statistical analysis

All analyses in this study will be conducted according to the intention-to-treat principle. Student's t-test is performed for normally distributed continuous variables while Wilcoxon signed rank test is for non-normally distributed data. The chi-square test or Fisher exact test is used for categorical variables. A two-sided P-value  $< 0.05$  is considered statistically significant.

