### **3. Aim**

This a multicenter, prospective, randomized, controlled trial which enrolling patients with HF, left ventricular ejection fraction (LVEF)  $\leq 35\%$ , and LBBB. Patients will be randomly assigned in a 1:1 ratio to receive either LBBP or BVP. The clinical endpoints (including primary and secondary endpoints) will be compared between the

two groups to evaluate the effectiveness and safety, in order to provide new treatment methods for such patients and improve their prognosis.

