## **3. Study Design**

This a multicenter, prospective, randomized, controlled trial which enrolling patients with HF, left ventricular ejection fraction (LVEF)  $\leq 35\%$ , and left bundle branch block (LBBB). Patients will be randomly assigned in a 1:1 ratio to receive either LBBP or BVP. Follow-up visits will be conducted at 1 month, 3 months, 6 months and every 6 months thereafter after surgery to evaluate the clinical endpoints (including primary and secondary endpoints) of the two groups.

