## 8.4 Statistical analysis of the endpoints

For the clinical endpoint, Kaplan-Meier (KM) survival curve and log-rank test are performed to compare the time-to-event between LBBP and BVP.

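### The plan names a paired test (Wilcoxon signed rank) for non-normal continuous data although the two arms are independent; it needs correcting, but no listed endpoint depends on it

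*Supplement*

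**What the plan says.** SAP 8.3 gives a pair of rules for continuous data: "Student's t-test is performed for normally distributed continuous variables", and "Wilcoxon signed rank test is for non-normally distributed data". Protocol v1.1 section 11.2 has the same sentence. Neither document says whether the t-test is paired or unpaired, and neither names a rank-sum or Mann-Whitney test anywhere.

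The design is two parallel arms. SAP section 3 reads: "Patients will be randomly assigned in a 1:1 ratio to receive either LBBP or BVP". Section 3 of the protocol gives the purpose as a comparison of the two groups on the primary and secondary endpoints. No matching of patients is described, and no within-patient analysis is specified.

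The clinical endpoint has its own rule in SAP 8.4: "Kaplan-Meier (KM) survival curve and log-rank test are performed to compare the time-to-event between LBBP and BVP". Categorical variables go to chi-square or Fisher's exact test (SAP 8.3).

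**The concern.** The signed-rank test works on differences within pairs. A patient in the LBBP arm has no natural partner in the BVP arm, so there are no differences to rank. The sentence sets this test beside Student's t-test and just before the tests for categorical variables, in a trial whose aim is to compare two groups. The natural reading is therefore that it is meant for between-arm comparisons.

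An analyst who followed the text literally would have to pair patients by their position in the file. For a skewed variable such as pacing threshold, the reported P-value would then depend partly on how the data set happened to be sorted. An analyst who recognised the mismatch would have to choose another test without support from the plan.

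**Working it through.** The plan gives no figure to reproduce here. The check has two parts: a reading of which analyses the sentence governs, and a look at how the named test behaves on two independent arms.

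**1. What the sentence governs**

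| Variable | Rule that applies | Affected? |
|---|---|---|
| Primary composite (death or HF hospitalization) | Kaplan-Meier and log-rank, SAP 8.4 | No |
| All-cause mortality and HF hospitalization separately | Kaplan-Meier and log-rank, SAP 8.4 | No |
| Echocardiographic response and super-response at 6 months | Rates, so chi-square or Fisher, SAP 8.3 | No |
| QRS duration, pacing threshold, LVEF, LVEDD, LVESD, age (protocol section 7) | t-test or signed rank, SAP 8.3 | Yes, if judged non-normal |

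The sample size rests on event rates (SAP 8.1), so it is not affected either.

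**2. Unequal arms**

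Inputs: 100 patients per arm and 10% dropout (SAP 8.1). Assumption: dropout is independent between patients and equally likely in each arm.

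- Variance of the number lost in one arm: 100 × 0.10 × 0.90 = 9.
- Variance of the difference between arms: 9 + 9 = 18.
- Chance that both arms lose exactly the same number: about 1/√(2π × 18) = 1/10.63 = 0.094. The exact binomial sum is also 0.094.

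So at follow-up the arms would differ in size about 91% of the time (1 − 0.094 = 0.906). With unequal numbers the test has no value: a trial run in scipy with 100 against 97 observations stopped with an error.

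**3. Equal arms**

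Assumption: lognormal data, 100 per arm. The documents give no distribution for any continuous variable, so shape and shift are illustrative. There were 5,000 replicates, two-sided 5% level, log-scale SD 1.

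| Setting | Signed rank, rejected | Rank-sum, rejected |
|---|---|---|
| No difference, random row order | 5.1% | 5.0% |
| Log-scale shift of 0.4 SD, random row order | 72.8% | 77.5% |
| No difference, each arm sorted by value before pairing | 81% | 5.1% |

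The loss of power is 77.5 − 72.8 = 4.7 percentage points. The third row is an extreme case. It shows that the nominal error rate holds only while row order is unrelated to the measured value.

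**4. Dependence on row order**

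Two simulated data sets were each held fixed and re-paired at random 2,000 times.

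| Data set (lognormal, 100 per arm) | Rank-sum P | Signed-rank P: lowest, median, highest | Pairings with P < 0.05 |
|---|---|---|---|
| Log-mean 0 and 0.15, SD 0.5 | 0.032 | 0.0026, 0.034, 0.174 | 76% |
| Log-mean 0 and 0.3, SD 1 | 0.019 | 0.0025, 0.048, 0.27 | 53% |

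The rank-sum test gives one P-value whatever the order of the file.

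**5. The other reading**

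Protocol section 7 collects data that are naturally paired within a patient: intrinsic and paced QRS duration, and pacing threshold and echocardiographic measures at implantation and follow-up. Signed rank would suit changes in these. On that reading the named test is sound for its purpose, but nothing in either document says how a non-normal variable is compared between LBBP and BVP.

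**The case against.** The strongest reply has four parts.

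- **The text does not say between arms.** This is correct. That use is inferred from the two-arm design, the t-test alongside it and the absence of any planned within-patient analysis. The inference is strong, and the within-patient reading still leaves a gap, so the sentence needs changing on either reading.
- **It is probably a naming slip for the rank-sum test.** This is plausible and may be the simplest explanation. It does not remove the problem, because the plan is the pre-specified reference and says something else in both documents.
- **Little harm would follow.** This largely stands. With random row order the type I error stays near 5%, and in the first fixed data set the median signed-rank P (0.034) is close to the rank-sum P (0.032). With unequal arms the mismatch would probably be noticed, because the test does not run. The percentages of pairings below 0.05 come from two assumed data sets with P-values close to the threshold. They illustrate the mechanism and do not measure expected harm.
- **No endpoint turns on it.** This stands in full. Continuous change in LVEF or LV diameter is not a listed endpoint; only the response rates are.

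A reader might infer that every P-value from this rule would be invalid, or that the trial's main conclusions are at risk. The documents support neither. The accurate description is that the test is not computable with unequal arms, and otherwise depends on arbitrary order and has somewhat less power.

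**Conclusion.** The rule is wrong as written, and its reach is minor. Both current documents name a one-sample or paired test as the only option for non-normal continuous data in a trial of two independent arms, and no test suited to that comparison is named.

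The consequences are confined to non-normal baseline, procedural and follow-up measurements. Their size is modest: a between-arm result that usually cannot be produced at follow-up (arms unequal about 91% of the time under the dropout assumption), or one that varies with row order and loses about 5 points of power in the assumed lognormal example. Those two figures rest on the stated assumptions. The mismatch between test and design does not. The primary endpoint, all listed secondary endpoints and the sample size are unaffected, so this is a wording correction and not a reason to doubt the main analysis.

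**What to change.** In SAP 8.3 and protocol section 11.2, name the Wilcoxon rank-sum (Mann-Whitney U) test for between-arm comparisons of non-normal continuous variables, and state that the t-test used between arms is the independent-samples form. Keep the signed-rank test only if a within-patient change is to be analysed, and then say which variables and time points it covers.

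Optionally, report median and interquartile range for variables analysed by rank methods. SAP 8.2 and protocol 11.2 currently give mean and SD for all continuous variables. That is a matter of presentation and does not affect any P-value.

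The cost is a sentence or two in each document. Sample size, data collection and trial conduct do not change.

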| Title             | Comparison of left bundle branch pacing and (LBBP) biventricular pacing (BVP) in the treatment of chronic systolic heart failure (HF) with left bundle branch block (LBBB): a multicenter, prospective, randomized, controlled trial                                                                                                                                                                                                                                                                                                                                                                                                                                                                                                                                                                                                                                                                                                                          |
| Aim               | To evaluate the effectiveness and safety of LBBP versus BVP.                                                                                                                                                                                                                                                                                                                                                                                                                                                                                                                                                                                                                                                                                                                                                                                                                                                                                                  |

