## **8. Safety assessment**

Procedure related complications including pneumothorax, pocket infection, lead dislodgement requiring revision, increased pacing threshold  $> 3 \text{ V}/0.5\text{ms}$  and pericardial tamponade will be documented as safety assessment during follow-up.

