## 11.2 Statistical analysis

All analyses in this study will be conducted according to the intention-to-treat principle. Continuous variables are described as mean  $\pm$  SD and categorical variables are described as frequencies or percentages. Student's t-test is performed for normally distributed continuous variables while Wilcoxon signed rank test is for non-normally distributed data. The chi-square test or Fisher exact test is used for categorical variables. For the clinical endpoint, Kaplan-Meier (KM) survival curve and log-rank test are performed to compare the time-to-event between LBBP and BVP. Subgroup analyses of the relationship between the primary endpoint and the baseline characteristics including age, sex, etiology, comorbidities, QRS duration, NYHA class, and left ventricular ejection fraction will be conducted. A two-sided P-value  $< 0.05$  is considered statistically significant. All statistical analyses are performed using SPSS Statistics version 22.0 (IBM Corporation, Armonk, NY).

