## **2. Study Objectives**

This study aims to evaluate the clinical outcomes of left bundle branch pacing (LBBP) versus biventricular pacing (BVP).

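### Safety against BVP is a stated aim, but for procedure-related complications the plan offers only percentages and a generic P<0.05 test, with no estimated difference or interval

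*Supplement*

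**What the plan says.** Protocol v1.1 gives the aim in its Summary as "To evaluate the effectiveness and safety of LBBP versus BVP". Section 3 (Aim) ties both parts to a between-arm comparison of the primary and secondary endpoints; its wording is "two groups to evaluate the effectiveness and safety, in order to provide new treatment methods for such patients and improve their prognosis".

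Safety itself is set out in protocol section 8: "Procedure related complications including pneumothorax, pocket infection, lead dislodgement requiring revision", together with a raised pacing threshold and pericardial tamponade, "will be documented as safety assessment during follow-up". These complications do not appear among the primary or secondary endpoints in protocol section 9 or in the SAP's endpoint section. A masked committee adjudicates safety as well as efficacy end points (protocol 4.2, SAP section 5).

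The SAP has no section on safety analysis. The rules that would apply to complication counts are the general ones. For description, SAP 8.2 has "categorical variables are described as frequencies or percentages". For testing, SAP 8.3 has "The chi-square test or Fisher exact test is used for categorical variables. A two-sided P-value $< 0.05$ is considered statistically significant", and protocol 11.2 gives the same test rule. No risk difference, confidence interval or margin is named for complications. The sample size (protocol 11.1, SAP 8.1) concerns the primary composite only: 10% v 25%, with 100 patients per arm as the final size.

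**The concern.** The complications are yes/no events at procedure or during follow-up. A test sized for a 15-point difference in an efficacy composite has little chance of detecting a moderate difference in less common events. When it does not reach P<0.05, the P-value does not tell the reader how large an excess of complications remains compatible with the data. Percentages per arm do not say so either, because they carry no statement of uncertainty.

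This matters because the trial is meant to support LBBP as a new treatment option. A clinician weighing it against BVP needs to know what excess of pneumothorax, infection, lead revision and the like the trial can rule out. As written, the plan gives the author of the report no prespecified quantity that answers this.

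**Working it through.** **Inputs**
- Patients per arm: 100 (protocol 11.1, SAP 8.1). With the plan's 10% dropout: 90.
- Test: chi-square or Fisher exact, two-sided, significant if P<0.05 (SAP 8.3).
- Complication rates: not given in either document. **Assumed** reference rates of 2% to 15%, with the other arm at double the rate.

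The plan states no power or size for safety, so there is no safety figure to reproduce. To calibrate the method, take the planned efficacy rates first.

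**Step 1. Normal approximation, n per arm**

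Power ≈ Φ{ [Δ − 1.96·√(2p̄(1−p̄)/n)] / √[(p₁(1−p₁)+p₂(1−p₂))/n] }

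- Efficacy, 10% v 25%, n = 100, before any dropout or crossover: p̄ = 0.175; (0.150 − 1.96 × 0.0537)/0.0527 = 0.85; power 0.80.
- Complications, assumed 5% v 10%, n = 100: p̄ = 0.075; (0.050 − 1.96 × 0.0373)/0.0371 = −0.62; power 0.27, so a miss rate of 73%.

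**Step 2. Exact enumeration**

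For small counts the approximation is rough, so all 2×2 tables were enumerated. The miss rate is the sum of Bin(i; n, p₁)·Bin(j; n, p₂) over tables with P ≥ 0.05, for Pearson chi-square without continuity correction and for two-sided Fisher.

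| Assumed rates | n per arm | Missed, chi-square | Missed, Fisher |
|---|---|---|---|
| 2% v 4% | 100 | 89% | 96% |
| 3% v 6% | 100 | 85% | 91% |
| 5% v 10% | 100 | 73% | 81% |
| 10% v 20% | 100 | 48% | 56% |
| 15% v 30% | 100 | 27% | 33% |
| 5% v 15% (tripling) | 100 | 32% | 41% |
| 5% v 10% | 90 | 76% | 83% |

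The two columns differ by choice of test. The uncertainty about the true rate is the spread down the rows, and it is much larger. Any single type of complication is no more frequent than the total, so the tests by type sit at or above the corresponding row for the total.

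**Step 3. What an interval adds**

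Take 10/100 on LBBP and 5/100 on BVP. The pooled rate is 0.075 and z = 0.05/0.0373 = 1.34, so chi-square P = 0.18; Fisher P = 0.28. Both would be reported as not significant.

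The Wilson 95% limits are 5.5% to 17.4% for 10/100 and 2.2% to 11.2% for 5/100. Newcombe's interval combines them (unrounded limits used):
- lower: 5.0 − √[(10 − 5.52)² + (11.18 − 5)²] = −2.6 points
- upper: 5.0 + √[(17.44 − 10)² + (5 − 2.15)²] = +13.0 points

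The data would be compatible with an excess of up to 13 points, which the P-value does not show.

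With equal counts of 5/100 in each arm, the half-width is √[(5 − 2.15)² + (11.18 − 5)²] = 6.8 points. Even identical observed rates leave an excess of nearly 7 points open.

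**The case against.** Four arguments can be made for the plan.

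First, it never says that a non-significant result will be taken as comparable safety. The aim is to evaluate, the complications are to be documented, and SAP 8.3 only defines when a result is called significant. This stands. A reader might infer that the trial intends to declare equal safety from P>0.05, but no section says so. The point is a missing analysis and a foreseeable misreading, not a false decision rule.

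Second, the test is not the only thing serving the safety aim. Protocol section 3 ties the aim to the primary and secondary endpoints; all-cause mortality is among these and is compared by Kaplan-Meier and log-rank. This also stands, but the listed complications are not among those endpoints, so that analysis does not reach them.

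Third, the complication rates are assumptions. It is tempting to take the 73% / 81% from 5% v 10% as a property of the design, or to say that a doubling would be missed most of the time whatever the rate. The documents support neither: at 15% v 30% the miss rate falls to 27% / 33%, and at 10% v 20% it is about half.

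Fourth, the lack of intervals is general across the SAP, low power for complications is ordinary in a trial sized on efficacy, and anyone could compute an interval from the published counts. All true. But an interval that the plan does not name may not be reported, and the wording of the safety conclusion would be left to the time of reporting.

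**Conclusion.** The point holds as a gap in the analysis of a stated aim. For procedure-related complications the plan provides percentages and a general significance test, and neither shows how much excess harm the data leave open. How often that test would miss a doubling depends on a rate that the documents do not give: from 89% / 96% (chi-square / Fisher) at an assumed 2% v 4% down to 27% / 33% at 15% v 30%, with 100 per arm and complete data. Across that range a non-significant P is weak evidence on relative safety, and it is very weak at the lower rates.

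The primary analysis is untouched. The point does not claim that the trial should have been powered for complications, nor that the plan commits to reading non-significance as safety. It is worth changing because a more informative method is available from data already being collected.

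**What to change.** In SAP 8.3 and protocol 11.2, add a safety paragraph that:
1. reports the risk difference, LBBP minus BVP, with a two-sided 95% confidence interval (Newcombe or Miettinen-Nurminen), for patients with any procedure-related complication and for each type listed in protocol section 8;
2. words the safety conclusion by the excess that the interval does and does not exclude;
3. states that P>0.05 will not be taken as evidence of equal safety.

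The cost is a few sentences and a handful of interval calculations. No margin, extra patients or new data are needed. Powering the test instead would be out of proportion: 80% power for an assumed 5% v 10% takes 435 per arm. The downside is small. The intervals will be wide, about ±7 points at 5/100 v 5/100, and the safety statement will be more cautious.
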